### Recruitment

The ad hoc sample was constituted by recruiting potential participants via a variety of parallel channels. The recruitment process was centered on a study website that advertised participation and provided access to the study registration portal. First, precommitted companies were contacted and reminded of their participation. These companies were provided with the necessary information and access data for the registration portal for their employees. In addition to the previously committed companies, further companies were contacted and selected ad hoc from web-based registers. The professional network of the members of the study team was also addressed. Moreover, the public was made aware of the study through the dissemination of flyers in public spaces and on social and traditional media platforms. These flyers were placed in locations frequented by the public, including public areas and local businesses, as well as distributed via direct mail in the region of Salzburg and neighboring German towns. Dedicated social media accounts were set up on Facebook (Meta Platforms, Inc) and Instagram (Meta Platforms, Inc), which used public relations strategies that extended beyond the dissemination of study-related information, such as sharing posts on general information on stress management, to achieve a broader reach. The study accounts were used to contact relevant social media groups, including those of employees and individuals with an interest in research or stress. In addition, individuals who regularly posted on work-related topics were also contacted. Similarly, articles on the Relax project were published in traditional regional and national newspapers with a specific reference to the study.

The registration portal directed respondents to a web-based screening that inquired about the inclusion and exclusion criteria, as well as basic demographic data, including age, gender, and current employment sector. The collection of demographic data was undertaken to ensure the resulting sample was representative of the target population.

### Randomization

The randomization process was conducted midway through the study, following the scheduled break. No data from P1 were used to balance the randomization in any way. The participants were randomly assigned to the groups *local* and *global*. For the group *local*, the intervention weight matrix was primarily affected by participants’ own ratings, while the ratings of all participants affected the weights for the group *global*. The group *local* was regarded as the group with greater personalization than the group *global*, given that the personalization in question was based on the individual inputs.

The participants were not informed of their group allocation, which meant that they were considered blinded. As the randomization was conducted by a separate subgroup of the study team from those involved in the study itself and the data analysis, the latter 2 parts of the study can also be described as double blinded. The evaluation of the data in pseudonymized form further enhanced this aspect of independence.

### App Intervention

The intervention consisted of the use of the system of the Relax app and the wearable sensor developed in the Relax project. The participants were encouraged to use the system daily in P1 and P2. To accommodate the planned technical adjustments that will be made throughout the course of the study, all participants will be required to commence the study and complete the phases simultaneously.

The Relax app was developed based on a predefined mock design at the kickoff of the Relax project. This design was crafted with future projects in mind, ensuring long-term usability for data collection across several subsequent studies. The data management plan adhered to the European Union regulations. Bluetooth Low Energy (Bluetooth SIG) facilitated communication between the device and the phone, while REST interfaces enabled data exchange between the phone and the database.

The app interface consisted of several areas: the dashboard, the questionnaires, the interventions, calendar page, support page, user information, and an overview of the sensor data (provided in P2). In the dashboard, participants could check the status of the connection and synchronization of the sensor and monitor their study’s progress. For the questionnaires, profile and daily questionnaires were available. The profile questionnaires consisted of a series of 7 diagnostic measurements about living and working conditions, technological competence, work-related and everyday stressors, risk factors, resources, coping strategies, and consequences of stress. The profile data were designed to be administered in the first week of P1 to serve as a source of personal information for personalizing the interventions in subsequent weeks of the study. However, due to technical barriers, this information could not be used for further personalization.

The daily questionnaires consisted of morning and evening questionnaires and interval questionnaires during the day. The morning questionnaires included items on the quality of sleep during the previous night, current state and experiences and expected stress for the day. The evening questionnaire included questions about chronic stress, the current state and experiences, and summarized experiences of the day. The interval questionnaires asked about the current state and experiences and the state and experiences at the time of the last stressful event, if any. Participants were required to complete the morning and evening questionnaires and at least 2 interval questionnaires each day. They received daily reminders for the morning and evening questionnaires. The interval questionnaires were to be completed approximately 4 hours apart at the latest. This interval ensured that the questionnaires could be completed smoothly, even on participants’ busy working days. Participants were reminded several times a day to complete the interval questionnaires: twice in P1 (noon and 3 PM) and 3 times in P2 (11 AM, 2 PM, and 5 PM).

In addition to the daily use of the app, the sensor was to be worn to record physiological stress. The Polar Verity Sense (VS; Polar Electro OY), a wristband photoplethysmography sensor with an integrated inertial measurement unit from which various HRV parameters can be derived, was used for this purpose. The sensor was to be worn day and night in P1 and P2. Participants were instructed to take a maximum of two 30-minute breaks per day to avoid overstimulation and recharge the battery. It was possible to limit the duration of use individually if they felt uncomfortable, for example, to take it off at night. None of the participants took up this offer.

From the second week of the study in P1, interventions were triggered on the basis of individual stress information. On the one hand, a trigger was immediately released when (very) high stress was subjectively noted within the daily questionnaires. On the other hand, a trigger was released from objective sensor data. Multiple HRV metrics were calculated from measured sensor data based on 5-minute intervals. A stress intervention was triggered if (1) both the root mean square of successive differences (RMSSD) and the low frequency (LF) to high frequency (HF) ratio exceeded a predefined absolute threshold (deceded for RMSSD; exceeded for LF/HF ratio), (2) both metrics were among the 25% most significant values for the individual within a 24-hour window, and (3) both conditions held for 2 consecutive 5-minute time intervals.

From the trigger, a notification displayed in each area of the app provided access to the decision tree, which used various questions about the circumstances of the current stress experience to offer the optimal individual intervention. The main areas of the decision tree were external stressors, internal stressors, and indirect stress-related areas. For external stressors, the focus was on a dichotomy between occupational and other stressors, while for other stressors, it was noted that the Relax project only addressed occupational stress, so the participants were redirected to the top level of the decision tree. Internal stressors were divided into amplifiers, emotions, reactions, and resilience. The peripheral areas were divided into prevention and further information. All of these areas were further specified by the participants through up to 4 levels of predefined pathways. At the end of each path, there were several possible interventions.

The possible interventions were weighted differently depending on the end point of the pathway. The weights ranged from 0 to 1, with a higher weight increasing the likelihood of allocation. In the preliminary stages of the project, the initial weights were set according to the expert opinion of the development team. After P1, the initial weights for intervention selection were adapted based on all available user interactions. Popular intervention for a specific context received increased weights, thus a higher probability of being chosen in the subsequent context. Within P2, the weights of these mappings were adapted instantly for each intervention feedback.

The choice of intervention was made automatically by the system on the basis of the random weighted selection. At each node of the pathway, participants had the opportunity to immediately choose the weighted random selection of an intervention.

The 179 interventions were drawn from various areas of CBT, including psychoeducation, skills and attitude training, and relaxation and health habits. The interventions were designed as microinterventions that could be completed in a short period so that they could be easily integrated into everyday work life. Presentation formats varied across interventions depending on their applicability. These included simple text or tables with information, task prompts with a description and call to action, assisted tasks where participants received automated live instructions or otherwise interacted live with the app, or open prompts where participants were given an open field for response and self-reflection. In addition, there were pseudochats where participants were guided through automated educational chat transcripts, audio, or video content. At the end of an intervention presentation, the intervention could be rated. These ratings changed the initial weights of the intervention accordingly. Over time, this resulted in an individualized weight pattern of possible interventions for each person. For economic reasons, the system could not reach the stage at which interventions were offered fully automatically, so participants used the decision tree to receive interventions until the end of the study. Multimedia Appendix 1 illustrates the intervention areas and their subtypes in relation to their initial probability of occurrence with respect to the various stressor types within the decision tree. This higher probability is represented by the presence of an initial weight >0.5 (range from 0.0 to 1.0). In addition, Multimedia Appendix 1 depicts the presentation formats applied to these intervention areas and subtypes, as well as their quantities.

The level of individualization of interventions in the respective experimental group was characterized by a variation in automatic individualization with regard to the interventions offered by the learning agent. Due to intentionally high α values during the adjustment of the intervention weight matrix, the *local* group had the possibility of significantly influencing their intervention delivery within 3 weeks, while the group *global* would only perceive minor changes. α-local describes the extent to which a rating changed the weight of an intervention for a single user. For the group *global*, it was set to 1.0 (no change to the user’s own weight), and for the group *local*, it was set to 2.1. The weights were adapted using the following formula: new_weight=old_weight * (alpha_local^old_weight). α-global describes the extent to which a rating changed the weight of an intervention for all users. It was set to 21 for both groups. The weights were adapted using the following formula: new_weight=old_weight *(alpha_global^(old_weight/number_of_users)).

Data entry was continuously monitored by the study team throughout the weeks. Participants were encouraged to continue their engagement through regular emails from the study team. It was expected that a general increase in adherence would be achieved as these messages were sent to all participants equally. If technical problems occurred, they were addressed individually via the app and generally via email. It is assumed that such individual correspondences would not add to the overall bias of the user experience since the individual disruption was already a bias, which is not uncommon in pilot studies. In P1, an update of the app was offered in the second week, which solved the technical problems that had arisen up to that point. Participants were given support to reinstall the app, and a self-help guide for the most common technical problems was offered. During the break between P1 and P2, additional technical difficulties were overcome by the study team, and when feasible and relevant, the participants’ input thus far was considered. Following this adaptation of the system in accordance with feedback, a graphical overview of the sensor data was made available in P2. This enabled the participants to maintain awareness of the data and its evolution over time.

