### Research Questions

This study aims to evaluate the prototype developed to date. The central research question of this evaluation is the effectiveness of the prototype in terms of the amount of stress reduction achieved by the participants. It is hypothesized that the greater the degree of personalization offered, the greater the reduction in stress. In addition, it was expected that all individuals would more or less experience an overall reduction in stress as a result of using the prototype. In addition to effectiveness, questions of usability and feasibility were addressed because of the pilot nature of the project approach and the research stage of the prototype at the time of the study. No hypotheses were formulated here, as the corresponding data were collected for exploratory purposes.

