**Primary**											
	Momentary emotional state	Arousal, valence		Daily EMA^a^ (morning, interval)		Internally created scale		7-point Likert scale		“My current mood is:”	
	Emotional state of last stress event	Arousal, valence		Daily EMA (interval)		Internally created scale		7-point Likert scale		“My mood was:”	
	Chronic stress	Lack of satisfaction, high demand, loss of control, ability to recover, and negative emotions		Daily EMA (interval)		Selected items from CSSS^b^ [53] and LKCS^c^ [54]		7-point Likert scale		“I couldn’t relax today.”	
	Work-related distress	Relationship, personal accountability, work-life balance, and workload		Pre-post online		VEDAS^d^ [55], online		6-point Likert scale		“Dealing with ambiguous or ‘delicate’ situations.”^e^	
	Work-related eustress	Relationship, personal accountability, work-life-balance, and workload		Pre-post online		VEDAS [55], online		6-point Likert scale		“Dealing with ambiguous or ‘delicate’ situations.”^e^	
	Satisfaction	Overall satisfaction, workday adaptability, exertion due to EMA, and exertion due to sensor handling		Pre-post online		CSAT^f^ [56], internally extended), online		5-point Likert scale		“How would you rate your overall satisfaction with Relax?”	
	Usability	—		Pre-post online		SUS^g^ [57], online		5-point Likert scale		“I found using the Relax app unnecessarily complicated.”	
	HRV^h^	SDRR^i^, RMSDD^j^, and LF^k^/HF^l^		Continuously		Polar VS^m^		Passive		—^n^	

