#### Primary Outcomes

First, primary outcomes were the emotional state over the course of the study and self-reported experience of chronic stress. On the one hand, levels of emotional states and stress were recorded daily using the ecological momentary assessment (EMA) technique. The data obtained from the daily subjective interval, morning, and evening interval questionnaires were used as a diagnostic tool. These questionnaires were developed internally, with established psychometric instruments used in certain cases. A team of experts was responsible for selecting the items for the internally developed instruments, some of which were commonly used items for the topics in question. Emotional state was assessed on the basis of the 2 dimensions: arousal and valence. In the interval questionnaire, in addition to the current state experienced at the time of entry, the state at a possible last stress event was also recorded in a similar manner.

The experience of chronic stress was evaluated using the evening questionnaire, which included items from the Chronic Stress Screening Scale [53] and the Leipzig Screening Questionnaire on Chronic Stress [54]. The Chronic Stress Screening Scale items assessed feelings of lack of satisfaction and high demands, while the Leipzig Screening Questionnaire on Chronic Stress items focused on experiences of loss of control, inability to recover, and negative emotions. The EMA questionnaires were each scored on a 7-point Likert scale. Conversely, chronic stress was evaluated using the Valencia Eustress-Distress Appraisal Scale [55] at the following time points after P1 and P2 in the web-based questionnaire. The questionnaire was used to distinguish between work-related distress and eustress, as well as to evaluate the subscales of relationship, personal accountability, work-life balance, and workload. A 6-point Likert scale was used in line with the original instrument.

Second, the physiological stress parameters, as measured by the Polar VS sensor, were recorded as primary outcomes. Similarly, the continuous data from the app use were used as an outcome. The stress parameters were HRV variables: SD of r-r-intervals, which is a direct measure of HRV; RMSSD, which is a measure of the parasympathetic recovery capacity; and LF/HF, which is the ratio of the balance between the sympathetic and parasympathetic nervous systems in favor of the latter.

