### Statistical Analysis

To statistically analyze the central evaluation questions of the prototype developed in the Relax project in terms of its efficacy in reducing stress in the workplace, different models will be constructed. First, the difference between the groups and thus the degree of individualization by the app will be determined. Second, the pre-post design will be used to ascertain whether the individuals exhibited a reduction in stress over time. These 2 approaches will use all stress-relevant outcomes to make assertions about the work stress of the individuals, namely the emotional states, self-reports on chronic stress as well as distress and eustress, and the physiological parameters. Linear mixed models will be used for the effectiveness analyses.

To address the usability and feasibility of the prototype, the data obtained from the satisfaction and usability scales will be used. These will also be analyzed between the groups and in the pre-post design. Exploratory analyses will test the secondary outcomes for possible effects. Additional moderation and mediation analyses will be possible here, in which the variables from the demographic and profile surveys could also be used. It is anticipated that the qualitative data from the user feedback will provide information about the specific background of the participants’ usability ratings.

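### The primary outcome on emotional state at the last stress event exists only where an event is reported, so used alone as effectiveness evidence it is open to selection bias

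*Protocol article*

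**What the plan says.** Table 1 of the protocol article lists "Emotional state of last stress event" (arousal and valence, 7-point scale, interval questionnaire) among the primary outcomes. The App Intervention section says that the interval questionnaire covers "the state and experiences at the time of the last stressful event, if any". The Primary Outcomes section repeats the condition: "the state at a possible last stress event was also recorded in a similar manner".

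The Statistical Analysis section sets out two effectiveness comparisons, between groups and pre-post, and states: "These 2 approaches will use all stress-relevant outcomes to make assertions about the work stress of the individuals, namely the emotional states". It adds: "Linear mixed models will be used for the effectiveness analyses". The Data Management section reduces daily data to weekly means and excludes records with more than 80% missing data.

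On timing, the Randomization section says: "The randomization process was conducted midway through the study, following the scheduled break". Table 2 shows the interval questionnaire running in both the first phase (P1) and P2. The App Intervention section gives two interval reminders per day in P1 and three in P2.

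**The concern.** A value of this outcome exists only when a participant reports a stressful event. An interval without an event has no value; it is undefined rather than missing. The weekly mean for this item is thus a mean over reported events, and a participant with no events in a week contributes nothing for that week. A linear mixed model does not repair this, because there is no unobserved value to recover. The 80% rule, as described, does not separate an event-free interval from an unanswered one.

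In P2 the condition arises after allocation. The study's hypothesis is that "the greater the degree of personalization offered, the greater the reduction in stress". If that is true, the more personalized group may well report fewer events, or a different mix of them. The comparison would then be between selected events, not between the groups as randomized. Benefit that takes the form of fewer events would drop out of the mean, and if mainly mild events disappear, the better arm would look worse.

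In the pre-post comparison the P1 values precede allocation, so randomization does not protect it in any case. Event reporting may change with time and app use, and the third daily reminder changes the prompting to report.

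**Working it through.** The article gives no event rate, no SD and no target difference for this outcome, so there is no figure of the plan to reproduce. Every input below is an assumption, chosen to show the size of the effect over a range. Scores are oriented so that higher is worse. The real item records arousal and valence, so this is a stand-in for whichever direction counts as worse.

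**1. Uniform shift with a reporting threshold.** Let the stress level be normal with SD 1 and mean μ, and let an event be reported when the level exceeds c. The mean among reported events is μ + φ(c − μ) / [1 − Φ(c − μ)], and the event rate is 1 − Φ(c − μ). Compare μ = 0 with μ = −0.30, a true reduction of 0.30 SD.

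- c = 0: 0.798 against 0.698, a difference of 0.100 SD (33% of the truth).
- c = 0.5: 1.141 against 1.067, a difference of 0.074 SD (25%). The event rate falls from 30.9% to 21.2%.
- c = 1: 1.525 against 1.470, a difference of 0.055 SD (18%).

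Most of the benefit lies in the event rate, which is not a listed outcome. A larger shift gives the same picture. With SD 1.2, mean 4.0 falling to 3.4, and thresholds of 4.5, 5.0 and 5.5, the true change of −0.6 shows as −0.15, −0.11 and −0.09.

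**2. Selective loss of milder events.** Let event scores be normal with mean 4.5 and SD 1.2. One arm prevents a fraction p of the below-average events and nothing else changes. The below-average half has a mean 1.2 × √(2/π) = 0.957 below 4.5. The mean of the remaining events rises by (p/2) × 0.957 / (1 − p/2).

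- p = 10%: 0.05 × 0.957 / 0.95 = 0.05 points.
- p = 25%: 0.125 × 0.957 / 0.875 = 0.14 points.
- p = 50%: 0.25 × 0.957 / 0.75 = 0.32 points.

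This arm has fewer events, and its remaining events score worse.

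**3. Both mechanisms together.** Suppose that in one group 30% of intervals have a mild event (score 4), 10% a severe event (score 6), and the rest score 2. The mean given an event is (0.30 × 4 + 0.10 × 6) / 0.40 = 4.50. In the other group half of the mild events are prevented and every remaining event is 0.2 points milder. Its mean given an event is (0.15 × 3.8 + 0.10 × 5.8) / 0.25 = 4.60, which is 0.10 worse. Over all intervals the first group averages 1.20 + 0.60 + 0.60 × 2 = 3.00 and the second 0.57 + 0.58 + 0.75 × 2 = 2.65, an improvement of 0.35.

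**4. No change in reporting.** In the model of step 3, if the number and mix of events stay the same and each is 0.2 points milder, the conditional difference is −0.2, which is correct. The bias comes only from a change in how many or which events are reported.

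**The case against.** A reader might infer that this outcome is biased as a matter of fact, or that the trial's effectiveness conclusion is compromised. The document supports neither.

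- **The arms may not differ in event reporting.** Interventions follow a stress signal. Both groups have the same app, sensor, decision tree and pool of 179 interventions, and differ in how ratings update the selection weights. The hypothesis concerns stress reduction and does not mention event frequency. This stands: differential reporting is plausible under the hypothesis but not shown.
- **Part of the outcome precedes allocation.** This is correct for P1. The post-randomization argument applies to the P2 group comparison; the pre-post comparison has the separate problem of changing event reporting.
- **The sizes rest on assumptions.** They do, and a small change in event mix gives a small bias (0.05 points at 10% prevention).
- **Other outcomes carry the claim.** Momentary emotional state, chronic stress, VEDAS and HRV do not depend on an event report, so one of the eight primary rows in Table 1 is affected. The state a person reports under stress is also a legitimate question in its own right. Both points limit the consequence.
- **Handling of event-free intervals belongs in the analysis plan, and this is a pilot.** The modelling detail may well sit there. But the article itself fixes the conditional definition, the primary status and the use in both effectiveness comparisons, and that combination is what can mislead.

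**Conclusion.** The point holds as a risk attached to one primary outcome. The plan defines it only for reported events and commits to "use all stress-relevant outcomes to make assertions about the work stress of the individuals", between groups and pre-post. If personalization, time or the added reminder changes how many or which events are reported, the mean over those events can understate a true effect (0.06 to 0.10 SD shown for 0.30 SD) or point the wrong way (0.05 to 0.32 points worse when 10% to 50% of below-average events are prevented). These sizes depend on assumed thresholds, means and SDs, and on a simple worse-is-higher scale. If event reporting is the same across arms and phases, this selection bias does not arise. The stronger inference, that the trial as a whole would hide a real stress reduction, is not supported, because the other stress-related primary outcomes do not depend on an event report.

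**What to change.** - Do not use the event-conditional state on its own as evidence of stress reduction. Rest the emotional-state effectiveness claim on the momentary state, which is asked whether or not an event occurred.
- Report the event-conditional state descriptively, always beside a logistic mixed model of event reported (yes/no) over all completed interval questionnaires. Keep 'no event' apart from 'not answered' where the stored data allow it.
- Base any causal reading on the P2 group comparison. Interpret the P1 to P2 change in event rate in light of the move from two to three daily reminders.
- Report interval-questionnaire completion by arm and phase.
- Declare the change as made after data collection and before analysis. The Results section says that the analyses have yet to be carried out, so this is still possible.

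The cost is one extra model on data already collected, one fewer primary outcome, and a disclosed departure from the published outcome list. The event rate still depends on questionnaire completion, which may itself differ by arm or phase, and the separation of event-free from unanswered intervals depends on what the app stored.
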